#### Primary analysis

Descriptive statistics will be used to characterize the patients at cohort entry.

Time dependent cox proportional hazard analyses will be used to estimate the adjusted hazard ratio of developing obesity-related cancer when using gliclazide compared to other SUs (both individual and grouped as non-gliclazide SU). Exposure to SUs will be included as the cumulative number of years exposed to a specific SUs. Exposure status for SU will be updated annually. The primary analyses will be corrected for the previously mentioned confounders measured at baseline.

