An association between the class of SUs and increased overall cancer risk has also been reported [21–24]. Most previous studies are limited by methodological issues, for example many studies reported baseline SU use and did not account for duration of SU use [22–24]. There is also evidence suggesting within-class SU differences in cancer risk, where gliclazide use has been associated with a lower cancer risk [21–24]. There are several potential mechanistic explanations, one of which could be that gliclazide leads to a more selective glucose dependent insulin response and lower insulin levels. In what way and to what degree cancer risk is modified by different SUs in unclear and requires further investigation and confirmation.

Most evidence, however, is derived from small observational cohort studies and substantial knowledge gaps exist. This also holds true for the presumed favourable long-term cancer safety profile of gliclazide in particular. The relations between use of glucose lowering agents and cancer are complex and there is overlap in risk factors; for example, several glucose lowering agents have been associated with weight gain, which in itself has also been related to an increased cancer risk.

The primary aim of this study is to evaluate within-class SU differences in risk for obesity-related cancer (excluding non-melanoma skin cancers) accounting for weight changes during follow-up and drug exposure [6]. Secondary aims are to evaluate within-class SU differences concerning all cancers combined and the cancer risks of the five largest groups of site specific cancers (breast, colorectal, prostate, bladder and lung cancer) accounting for duration of drug use.

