#### Study endpoints

The primary outcome will be within-class SU difference in obesity-related cancer risk (see Table 1 for included cancers). The secondary outcomes will be all cancer risk (Table 2), site-specific cancer risk and the presence of a duration response relationship between SU use and cancer. Cancer sites of special interest will be specific cancers of the breast, colorectal, bladder, advanced prostate and lung cancer. Study endpoints will be evaluated for men and women separately.

**Table 1 Tab1:** Cancers included in primary endpoint obesity related cancer

Men	Women
Oesophageal (adenocarcinoma)	Oesophageal (adenocarcinoma)
Stomach cardia	Stomach cardia
Kidney	Kidney
Gallbladder	Gallbladder
Liver	Liver
Pancreatic	Pancreatic
Colorectal	Colorectal
Prostate cancer	Ovarian
	Breast
	Endometrial

**Table 2 Tab2:** Cancer excluded from secondary endpoint all cancer risk

Men (cancers excluded)	Women (cancers excluded)
Non-melanoma skin cancer	Non-melanoma skin cancer
Breast	Prostate
Ovarian	Male genital organs
Endometrial	
Female genital organs	

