#### Exposure

Patients will be considered unexposed to SUs until the time of the first SU prescription within ZODIAC. A one-year lag period will be accounted for. A lag period is necessary to take into account a latency time window and to minimise possible detection bias around the time of treatment initiation. Exposure to a SU will be classified according to one of the following, mutually exclusive, categories: gliclazide use, glimepiride use, tolbutamide use, glibenclamide use, non-SU use.

We aim to determine whether there are duration-response relationships between the use of SUs and obesity-related cancer incidence. Duration-response will be assessed in terms of cumulative duration of use, defined as the total number of years of use calculated by summing the durations of yearly prescriptions received between cohort entry and the time of the event and will be used as a time-dependent covariate.

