#### Secondary analyses

In a secondary analyses changes diabetes medication during follow-up will be accounted for. Time dependent cox proportional hazard analyses will be used to estimate the adjusted hazard ratio of developing all cancer when using gliclazide compared to other SUs (both individual and grouped as non-gliclazide SU). Exposure to confounders (including concurrent metformin and insulin use) will be handled as time varying variables where follow-up is available. The updated mean method will be used for HbA1c, BMI and serum creatinine. These analyses will be repeated to investigate the adjusted hazard ratio of breast, colorectal, prostate, bladder and lung cancer.

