## Discussion

This study will be the first large observational cohort study investigating differences in cancer risk within the class of SUs. An estimated 8% of the global population is known with T2D [29] and this could translate into an increased risk of cancer for an substantial amount of people. The prevalence of T2DM is expected to rise evermore, at least for the next decades [30]. A minimal change in cancer risk could result in a substantial change in the relative and even absolute number of patients diagnosed with cancer. If this study confirms the presence of within-class SU cancer risk differences, it could help patients and physicians in making a shared decision for a specific SU. This could contribute to quality of life of the patients as well as contribute to increasing effective care and cost-effectiveness of healthcare. If no differences are present, the safety, efficacy, and cost of SU will remain the only criteria for selecting the best SU.

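### The primary question covers differences among four sulfonylureas, but the primary analysis names only contrasts against gliclazide, leaving three of the six pairs without a direct estimate

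*Protocol article*

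**What the plan says.** - **Aim (Background).** "The primary aim of this study is to evaluate within-class SU differences in risk for obesity-related cancer".
- **Endpoint (Study endpoints).** "The primary outcome will be within-class SU difference in obesity-related cancer risk".
- **Exposure.** The mutually exclusive categories are "gliclazide use, glimepiride use, tolbutamide use, glibenclamide use, non-SU use", so the class consists of four drugs.
- **Primary analysis.** The hazard ratio to be estimated is that of "developing obesity-related cancer when using gliclazide compared to other SUs (both individual and grouped as non-gliclazide SU"). Exposure enters as a duration: "Exposure to SUs will be included as the cumulative number of years exposed to a specific SUs".
- **Secondary analyses.** The same structure is used for "developing all cancer when using gliclazide compared to other SUs (both individual and grouped as non-gliclazide SU") and is then repeated for the site-specific cancers.
- **Reason for the gliclazide reference (Background).** Earlier evidence is cited "where gliclazide use has been associated with a lower cancer risk".
- **Discussion.** "If no differences are present, the safety, efficacy, and cost of SU will remain the only criteria for selecting the best SU".

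No joint comparison of the four drugs is named, and neither is any contrast among glimepiride, tolbutamide and glibenclamide.

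**The concern.** The aim and the endpoint ask whether the SUs differ from one another. The named contrasts ask whether gliclazide differs from the others. These questions diverge most when gliclazide lies between a higher-risk and a lower-risk SU. Each gliclazide contrast then sees only part of the spread, and the pooled comparator mixes a drug above gliclazide with one below it. The largest difference in the class would appear nowhere in the results with its own estimate and interval. A reader choosing between, say, tolbutamide and glibenclamide would have to divide two reported hazard ratios and could not attach a confidence interval without their covariance.

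**Working it through.** **Which pairs are covered.** Four drugs give 4 × 3 / 2 = 6 pairs. The primary analysis names three (gliclazide against each other SU), plus one pooled contrast. The three pairs among the other SUs are not named.

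**Whether those differences are wholly outside the analysis.** Written as a contrast matrix on four drug effects, the three gliclazide contrasts have rank 3. Adding the three remaining pairs leaves the rank at 3. All three gliclazide hazard ratios equalling 1 is therefore the same null hypothesis as equality of all four drugs. Any difference among the other three implies that at least one of them differs from gliclazide. What is lost is power and direct estimation. Only the pooled contrast can cancel.

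**Size.** The document gives no event count, drug shares or effect sizes, so there is no figure to reproduce and all inputs below are assumptions. For simplicity the drugs are treated as four exposure groups, not as cumulative years.

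- Shares for gliclazide/glimepiride/tolbutamide/glibenclamide: 15/35/40/10%.
- Hazard ratios versus gliclazide: 1.00 (glimepiride), 0.85 (tolbutamide), 1.25 (glibenclamide).
- 800 events, two-sided 5%.

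Events are allocated in proportion to share × HR. The products are 0.15, 0.35, 0.34 and 0.125, with sum 0.965. This gives 124.4, 290.2, 281.9 and 103.6 events.

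SE(log HR) = √(1/e₁ + 1/e₂), and power = Φ(|log HR|/SE − 1.96) + Φ(−|log HR|/SE − 1.96).

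- Gliclazide vs tolbutamide: |log 0.85| = 0.163, SE 0.108, power 33%.
- Gliclazide vs glibenclamide: log 1.25 = 0.223, SE 0.133, power 39%.
- Gliclazide vs glimepiride: no difference assumed, 5%.
- Gliclazide vs pooled: HR = (0.35 + 0.34 + 0.125)/0.85 = 0.96, SE 0.098, power 7%.
- Glibenclamide vs tolbutamide (not named): HR 1.25/0.85 = 1.47, log 0.386, SE 0.115, power 92%.
- 3-df test: noncentrality Σ eᵢ(log HRᵢ − weighted mean)² = 12.0, power 84%.

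The fair comparator for the 3-df test is the chance that at least one of the three individual gliclazide contrasts is significant, obtained by simulating the four log hazards with variance 1/eᵢ. The last row needs an assumed split of the remaining half.

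| Shares (%), events | Gliclazide vs glimepiride, tolbutamide, glibenclamide | Pooled | At least one of three (Bonferroni) | 3-df test | Direct glibenclamide–tolbutamide |
|---|---|---|---|---|---|
| 15/35/40/10, 800 | 5, 33, 39 | 7 | 67 (42) | 84 | 92 |
| 15/35/40/10, 400 | 5, 19, 22 | 6 | 41 (21) | 52 | 66 |
| 25/25/25/25, 800 | 5, 34, 64 | 7 | 84 (63) | 93 | 97 |
| 50/20/20/10, 800 | 5, 38, 52 | 5 | 74 (52) | 69 | 84 |

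Entries are power in percent. If all four drugs are equal, the unadjusted at-least-one rule has a type I error of about 12% with the shares of the first row, against 5% for the 3-df test.

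**Other patterns.** With 100 events per drug and only one other SU differing (HR 1.5), at least one individual contrast is significant in 85% (69% with Bonferroni) and the 3-df test also has 85%. If all three other SUs have HR 1.3 versus gliclazide (shares as in the first row, 800 events), the pooled contrast has 67% and the 3-df test 50%.

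**The case against.** The strongest reply has four parts.

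**Coverage.** A reader might infer that differences among the other three SUs go untested. The rank argument shows otherwise: the individual gliclazide contrasts jointly span the four-drug null, and the cancelling problem belongs to the pooled contrast alone. This part of the reply stands in full. Setting single-contrast powers of 33% and 39% beside 84% would also make the loss look greater than it is; the fair figure is 67%.

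**Rationale.** The gliclazide reference follows from the Background, which describes earlier evidence and a possible mechanism. If gliclazide is indeed the drug that differs, the pooled contrast is the more powerful test (67% against 50%). This is a good reason not to replace the gliclazide contrasts with an overall test. It is no reason to omit the overall test.

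**Discussion.** A reader might infer that the protocol will report non-significant gliclazide contrasts as absence of any difference in the class. The sentence is a conditional remark about what would follow if no differences existed. It is not a decision rule, and the document does not say how absence would be judged.

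**Level of detail.** A joint test and further pairwise intervals are often left to an analysis plan, and one not shown here may contain them. That is fair for the test as such. But the Primary analysis section does more than stay silent: it says which comparisons will be made, and they are narrower than the aim and endpoint of the same article.

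**Conclusion.** The point holds as a mismatch between question and analysis, and it is minor. The aim, endpoint and exposure categories concern four drugs. The named contrasts leave three of six pairs without an estimate or interval and cover them only indirectly, usually with less power than a direct contrast when gliclazide lies between them. In the illustration that means 67% unadjusted (at about 12% type I error) or 42% with Bonferroni, against 84% for the overall test and 92% for the direct contrast.

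These figures rest on assumed shares, hazard ratios and event counts. The advantage of the 3-df test over unadjusted gliclazide contrasts is not general: it vanishes when only one other SU differs, and reverses (69% against 74%) when gliclazide has half the exposure. What does not depend on the assumptions is that the three remaining pairs get no hazard ratio or confidence interval. The documents do not support saying that these differences are untested, or that the protocol commits itself to a class-wide null conclusion.

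**What to change.** In the Primary analysis section, keep gliclazide versus each other SU and versus the pooled others as the directional hypothesis. Add, from the same fitted model:

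1. a 3-df Wald or likelihood-ratio test that the four SU coefficients are equal;
2. the three remaining pairwise hazard ratios (glimepiride–tolbutamide, glimepiride–glibenclamide, tolbutamide–glibenclamide) with confidence intervals.

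Base any class-wide statement of the kind in the Discussion on all six intervals, because a non-significant overall test alone does not show that differences are absent. Otherwise restrict the statement to gliclazide versus other SUs.

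The cost is about one sentence and a few lines of code, with no new data or model. The downside is one more test and three more intervals to report.

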#### Patient selection

The study cohort entry date and baseline date will be the date the patients started participation in the ZODIAC cohort.

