#### Exclusion

Patients treated with long-acting or mixed insulin before oral glucose lowering agents and those receiving insulin on top of SU at study entry will be excluded. Patients who received a cancer diagnosis before receiving a SU will be excluded. For the main analyses patients who switch medication within the class of SUs will be excluded at the time the switch occurs.

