#### Sensitivity analysis

Six sensitivity analyses will be planned for supporting the main analyses. Firstly, because the latency window is uncertain, the primary analyses for within-class differences will be repeated with lag periods of zero and two years. Secondly, the primary analysis will be repeated but the adjusting confounders will be measured at the year before first SU prescription. Thirdly, the main analysis will be repeated but with the exclusion of cancer events 1 year after initiation of a SU. Fourthly, to investigate the accuracy of our results the analysis will be repeated in patients in whom all data on medication are complete. Fifthly, to investigate the accuracy of our results the analysis will be repeated in patients who have no missing data on HbA1c, BMI and serum creatinine. Sixthly, to quantify the effect of patients switching medication within the class of SUs, an intention-to-treat analysis for patients who switch SUs will be performed.

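### The primary aim promises to account for weight change during follow-up, but no analysis of obesity-related cancer is clearly specified to do so

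*Protocol article*

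**What the plan says.** All references are to the protocol article.

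- **Background.** The primary aim is to compare SUs on obesity-related cancer, "accounting for weight changes during follow-up and drug exposure".
- **Patient selection.** "The study cohort entry date and baseline date will be the date the patients started participation in the ZODIAC cohort".
- **Exposure.** "Patients will be considered unexposed to SUs until the time of the first SU prescription within ZODIAC".
- **Primary analysis.** The outcome is obesity-related cancer. SU exposure enters as cumulative years, and "Exposure status for SU will be updated annually". For the covariates, "The primary analyses will be corrected for the previously mentioned confounders measured at baseline".
- **Secondary analyses.** "Time dependent cox proportional hazard analyses will be used to estimate the adjusted hazard ratio of developing all cancer when using gliclazide". Here confounders vary over time, and HbA1c, BMI and creatinine enter as updated means. The models are then repeated for five sites: lung, breast, bladder, prostate and colorectal.
- **Subgroup analyses.** BMI and HbA1c during follow-up are examined and interaction is tested. The outcome is given only as cancer.
- **Sensitivity analysis.** In the second of six, "the primary analysis will be repeated but the adjusting confounders will be measured at the year before first SU prescription".

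**The concern.** The aim and the model differ on a point that both state explicitly, so this is not a detail that a condensed article would leave to an analysis plan. Weight is the covariate that the Background singles out: glucose-lowering drugs are linked to weight gain, and weight gain to cancer. A reader of the published hazard ratio, told that the aim was to account for weight change, would take the estimate to be weight-adjusted. It would not be. If gliclazide users and users of other SUs gain weight differently, the baseline-adjusted and weight-adjusted hazard ratios answer different questions. The article does not say which one the primary endpoint is meant to answer.

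A second, smaller matter concerns timing. A comparison of one SU with another is confounded by the patient's state when the drug is chosen. The primary model uses the state at ZODIAC entry, which can be earlier.

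**Working it through.** The article gives no event count, power or effect size on this point, so there is no figure to reproduce. The check sets the sections side by side.

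**Step 1: which analysis of which outcome uses weight during follow-up?**

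| Analysis | Outcome | BMI | Weight-adjusted HR for the primary endpoint? |
|---|---|---|---|
| Primary | Obesity-related cancer | Value at ZODIAC entry | No |
| Secondary, time-varying | All cancer (1) and sites (5): 1 + 5 = 6 outcomes | Updated mean | Not specified: composite not named |
| Subgroup | Cancer, not further defined | During follow-up, interaction test | Not stated |
| Sensitivity 2 | As primary | Year before first SU prescription | No: nothing after SU start |
| Other five sensitivity analyses | As primary or main analysis | No change in how BMI is adjusted for | No |

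The other five sensitivity analyses vary the lag, drop early events, restrict to complete medication data, restrict to complete covariate data, and treat switchers by intention to treat. None adds weight during follow-up.

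**Step 2: could the primary model be read as already time-varying?** It is called time-dependent, but the annual updating is stated for SU exposure, and the confounders are then fixed at baseline. The Missing data section mentions the updated mean only as a fallback when multiple imputation cannot be used. That does not put follow-up BMI into the primary model.

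**Step 3: is the missing analysis feasible?** Yes. The Co-variates section says BMI, HbA1c and creatinine are collected at entry and every year after, and the model form already exists under Secondary analyses.

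**Step 4: how old can entry values be when an SU is started?** Participation can begin in January 1998 and follow-up ends on 31 December 2012, which spans 2012 − 1998 + 1 = 15 calendar years. In the extreme, entry values could be almost 15 years old at SU start. The distribution of the gap is not given. For patients who start at or near entry it is close to zero. Some patients are already on an SU at entry: the exclusion removes only part of them ("those receiving insulin on top of SU at study entry will be excluded"). For the rest, entry values come after the choice of drug and may already reflect it.

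**The case against.** **Baseline-only BMI is a defensible primary choice.** If SUs differ in their effect on weight, BMI after SU start is on the pathway from drug to cancer, and adjusting for it removes part of the effect. This stands. It is a reason to keep the baseline-adjusted hazard ratio and label it. It does not reconcile that model with an aim that promises to account for weight change.

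**The subgroup analysis may contain follow-up BMI, and its outcome is not restricted.** This also stands, and it is why the conclusion is limited to what is clearly specified. An interaction test still does not amount to a stated weight-adjusted estimate for the composite.

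**The better-timed confounders are already planned.** The second sensitivity analysis uses the year before the first SU prescription. Simply swapping it with the primary would create problems: patients already on an SU at entry have no pre-SU year within ZODIAC, and because follow-up starts at entry, fixed pre-SU values would place future information on earlier person-time unless time zero moved. So the timing point is secondary.

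Three stronger readings are tempting but not supported:

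- *That a given share of confounding remains.* Any percentage would need the correlation between entry values and values at SU start. The document gives none.
- *That calendar year and diabetes duration are out of date too.* The model includes year of entry and duration at entry. If time since entry is the time scale, which Follow-up implies but does not state, patients in a risk set share the same elapsed time, so adjusting for the entry values also accounts for current year and duration.
- *That updated covariates are unlagged.* The article states a one-year lag under Exposure and is silent on covariates. Silence is not a rule.

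**Conclusion.** The point holds as a mismatch between the stated primary aim and the specified analyses. The primary model adjusts for BMI at ZODIAC entry only. The six outcomes named for the updated-mean model do not include obesity-related cancer, and the subgroup analysis promises no weight-adjusted hazard ratio. As written, no planned analysis clearly delivers the weight-change part of the primary aim.

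Its effect on the hazard ratio cannot be computed: the article gives neither weight trajectories by SU nor the distribution of time from entry to SU start. A reader might infer that the primary hazard ratio is therefore biased. The document does not show that. As an estimate that leaves weight change after SU start unadjusted, the baseline-adjusted ratio may be sound, subject to the timing point. That point applies to HbA1c, BMI, creatinine and metformin use in patients who start an SU after entry, and it is partly met by the planned sensitivity analysis.

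**What to change.** 1. Add obesity-related cancer to the outcomes of the time-varying model under Secondary analyses.
2. State that updated-mean BMI, HbA1c and creatinine are lagged by the same year as exposure, so that weight loss from a cancer not yet diagnosed does not enter the adjustment.
3. Report two labelled hazard ratios for the primary endpoint: the baseline-adjusted one as the total effect and the time-updated one as the weight-adjusted effect. The second should not replace the first. Add the caveat that BMI after SU start may be a mediator affected by earlier exposure, so putting updated BMI into a Cox model does not by itself give a clean direct effect. A marginal structural model is an option.
4. If the weight-adjusted estimate is not wanted, remove the weight-change wording from the aim instead.
5. For confounder timing, report the analysis with pre-SU confounders alongside the primary result. Alternatively, update covariates up to SU start and hold them from there, keeping entry values for patients already on an SU at entry. This avoids future information on pre-SU person-time.

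The cost is wording, one extra model (fitted in men and women separately, as planned for the endpoints) and a second hazard ratio to interpret. No new data are needed. A marginal structural model, if chosen, would take more work.
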